### Adverse experiences and monitoring

Potential risks of both PGB and GBP have been well studied owing to their use for neuropathic conditions. These risks have been minimised by our exclusion criteria. Any SEs will be monitored weekly during follow-up phone calls and examinations. Close monitoring of other neurological pain medications will be done with patient diaries. SEs were quantified in a latest meta-analysis and given the rare SEs of both medications and their likely effectiveness, and the potential benefits outweigh the risks in this study [1].

During the recruitment period, a monitoring visit may be applicable. The responsible monitor will be a specialist neurosurgeon who is not involved in the conduct of the trial and is chair of the hospital patient safety committee. The purposes of monitoring are as follows:To ensure that the study is conducted according to the protocol and applicable guidelines and regulationsTo verify source data against data on the CRF and in the databaseTo check the security of stored dataTo confirm that the consent process, approved by the Townsville Hospital Human Research Ethics Committee, has been followed and to view a random sample of original signed consent formsTo review all serious adverse events (SAEs)

Interim data monitoring will take place in-house for review of safety and SEs. The trial may be stopped if more harm to patients is shown. The Pocock boundary will be used as the stopping rule, whereby after each set of 2n patient responses to a total of ‘K’ looks at the data. "2n" patient responses means there will be at least 2 interim analyses whereby the stopping rule can be enforced. This will be a group sequential approach whereby the critical boundary (*p* < 0.018) will be set at each look.

An adverse event is the appearance or worsening of any undesirable sign, symptom or medical condition occurring after starting the study, even if the event is not considered to be related to the investigational drug. Any SAE (defined as an event that is life-threatening or results in death, hospitalisation or significant disability) will be reported immediately to the relevant authorities (study monitor, ethics committee, data and safety monitoring board). If a potential relationship is suspected between the study drug and an SAE, then un-blinding to treatment allocation is indicated, and the participant will be withdrawn from PAGPROS.

Abnormal laboratory values or test results constitute adverse events only if they induce clinical signs or symptoms, are considered clinically significant or require therapy. The occurrence of adverse events should be sought by non-directive questioning of the patient at each visit during the study. Adverse events also may be detected when they are volunteered by the patient during or between visits or through physical examinations, laboratory tests or other assessments.

All adverse events will be recorded as follows:Severity grade: mild, moderate or severeRelationship to investigational drug: suspected/not suspectedDurationContinuation to an SAE

All adverse events will be treated appropriately. The action taken to treat the adverse event should be recorded. An SAE is defined as follows:Fatal or life-threateningResults in persistent or significant disability/incapacityConstitutes a congenital anomaly/birth defectRequires inpatient hospitalisation or prolongation of existing hospitalisation

To ensure patient safety, every SAE, regardless of suspected causality, occurring after the patient has provided informed consent and until 7 days after the patient has stopped study participation will be noted by expedited reporting to the Townsville Hospital and Health Service Human Research Ethics Committee.

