#### Secondary objective and outcome

Our secondary objective is to demonstrate if one drug (i.e., either GBP or PGB) demonstrates superiority over the other in terms of the frequency and severity of SEs in the treatment of sciatica. The key secondary outcome will be the record of frequency and severity of SEs. Details of SEs will be collected at weeks 4, 8, 10, 14 and 18. The most common SEs of PGB are dizziness and somnolence [11]. The most common SEs of these medications are dizziness (27%), drowsiness (22%) and decreased memory (20%) [10].

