### Randomisation and blinding

The trial pharmacist (un-blinded) will generate a randomisation code using a computer-derived permuted block with varying block size sequence. Manufacturing and preparation of the medication capsules will be performed by an external good manufacturing practice-accredited facility. The unblinded pharmacist will be involved in the preparation of the medication kits as per the randomisation schedule. The sequence will follow a 2 × 2 sequential design whereby participants will receive PGB first, then GBP (or vice versa), in a double-blinded fashion. Owing to the variability in regular dosage frequency between the medications (PGB twice daily, GBP thrice daily), study medication packs will contain three bottles each, correlating to the dosage times of morning, lunchtime and night, so as to maintain blinding. Medication packs pertaining to the PGB arm will have placebo incorporated as the lunchtime dose with all medications being indistinguishable. The randomisation schedule will remain concealed from other researchers. Placebo capsules will have an appearance identical to the active capsules. The randomisation process will ensure concealed allocation and blinding of the specialist, the participant and the outcome assessor.

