### Data collection

Data collection will be conducted by the study researchers via telephone, email or online at baseline (before medication commencement) and at weeks 4, 8, 10, 14 and 18. Week 10 data collection will act as the cross-over secondary baseline for analysis purposes. Data will be entered into CRFs by dedicated trained staff. Each participant will receive up to seven face-to-face or telephone consultations with the trial pharmacist to commence treatment, monitor progress and adjust the dose of the study medication over the 8-week treatment periods. These visits will also incorporate a medical evaluation and collection of primary and secondary outcomes. Participants will receive usual neurosurgical care independent of and parallel to PAGPROS.

The use of prior and continued analgesic medicines will be collected at baseline. Adherence to study medication will be documented through a self-reported daily medication diary and by counting the returned medicine compared with the prescribed regimen as recorded by the trial pharmacist. Participants will be asked to return used and unused study medications at each visit.

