## Discussion

The PAGPROS protocol presents the design and rationale for a double-blind, double-dummy, randomised cross-over trial comparing the efficacy of PGB with GBP in treating CS. Owing to the variability in regular dosage frequency between the medications (PGB twice daily, GBP thrice daily), study medication packs will contain three bottles each, correlating to the dosage times of morning, lunchtime and night, to maintain blinding. Medication packs pertaining to the PGB arm will have placebo incorporated as the lunchtime dose, with all medications being indistinguishable.

Thus, PAGPROS represents the first head-to-head study to determine the relative role of either PGB or GBP in the evidence-based medical management of CS. However, in addition to efficacy, PAGPROS will also determine the frequency and severity of SEs with PGB or GBP. Thus, PAGPROS will determine the ‘efficacy versus SE trade-off’ with each drug and whether differences in compliance rates result in consequences. For example, in a prior study with GBP in treating CS, 31% of patients ceased GBP within 1 week of treatment [10]. Moreover, efficacy was significantly less in those who experienced SEs in that study [10].

In PAGPROS, we will employ the HLOC to assess psychological functioning with PGB or GBP in CS. In particular, PAGPROS will explore the prognosis of each drug relating to questionnaire outcomes relating to patients’ insight into their psychological dysfunction. Thus, PAGPROS may determine deficits and provide information not actually reported as SEs by the patients themselves. This may prove to be an important aspect of the study. For example, a prior prospective cohort study with GBP in treating CS revealed that, of 23 different SE types amongst 53% of patients, more than half could have adversely affected the ability to drive a motor vehicle safely or even to maintain employment [10].

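### The side-effect comparison rests mainly on open questioning, and the text lets an unblinded pharmacist do the asking and grading despite promising a blinded assessor

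*Protocol article*

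**What the plan says.** All references are to the protocol article.

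- **Role of the data.** Secondary objective and outcome sets out to show whether one drug is superior to the other on side effects, and states: "The key secondary outcome will be the record of frequency and severity of SEs". On timing: "Details of SEs will be collected at weeks 4, 8, 10, 14 and 18". That section does not say how the details are obtained.
- **Method.** Adverse experiences and monitoring states: "The occurrence of adverse events should be sought by non-directive questioning of the patient at each visit during the study". The next sentence adds further routes: "Adverse events also may be detected when they are volunteered by the patient during or between visits or through physical examinations, laboratory tests" and other assessments. Earlier in the same section: "Any SEs will be monitored weekly during follow-up phone calls and examinations". Each event is graded mild, moderate or severe and judged as suspected or not suspected to be drug-related.
- **Who collects.** Randomisation and blinding promises a blinded outcome assessor, yet the same section says: "The trial pharmacist (un-blinded) will generate a randomisation code using a computer-derived permuted block with varying block size sequence". Data collection opens by assigning the work to the study researchers. It then says: "Each participant will receive up to seven face-to-face or telephone consultations with the trial pharmacist", and adds that both the primary and the secondary outcomes are gathered at those visits.

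**The concern.** Two features combine.

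First, an open-ended method suited to safety surveillance supplies a comparative endpoint. A within-patient contrast between drugs is sound only if the same effects are looked for in the same way in both periods. The protocol names effects it expects (dizziness 27%, drowsiness 22%, decreased memory 20%), but the method it states does not ask about them by name.

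Second, on one reading of Data collection, the person asking knows which drug the patient is taking. With an open question, that person decides how far to pursue a vague answer and which severity grade to record. Under Study treatment and Data collection, the same pharmacist also takes part in dose changes made for side effects, so the subject will come up in these consultations anyway.

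At stake is the key secondary result and the efficacy versus side-effect trade-off that the Discussion promises from it.

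**Working it through.** **1. Is there a planned figure to reproduce?** There is none for the side-effect comparison. The sample size (30 evaluable, 38 after drop-out, since 30 / 0.80 = 37.5) is for the pain score and is not affected. I use 30 pairs below only because that is the planned evaluable number.

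**2. Who collects, side by side.**
- Randomisation and blinding: the outcome assessor is blinded and the trial pharmacist is not.
- Data collection, opening: study researchers collect the data.
- Data collection, later: the pharmacist's consultations gather primary and secondary outcomes.

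These can be reconciled only if someone other than the pharmacist records the outcomes at those consultations, and the text does not say so. The sentence on non-directive questioning does not say who asks.

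**3. What imperfect capture does.** Let p1 and p2 be the true risks of any side effect in a period on each drug, and s1 and s2 the shares of affected periods that are recorded. The observed difference is s1·p1 − s2·p2.
- Equal capture (s1 = s2 = s) gives s·(p1 − p2). The difference shrinks but is never created.
- Equal risks (p1 = p2 = p) give p·(s1 − s2). Any difference is spurious.

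**4. Illustration.** Only the 53% risk on gabapentin is from the protocol (a prior cohort, cited in the Discussion and under Dosages). The following are my assumptions: the second drug's risk, the capture shares, a within-patient correlation φ = 0.3, independent recording in the two periods, and a two-sided 5% exact McNemar test on 30 pairs.

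The probability of an effect in both periods is p11 = p1·p2 + φ·√[p1(1−p1)·p2(1−p2)]. The observed discordant probabilities are b = s1·p1 − s1·s2·p11 and c = s2·p2 − s1·s2·p11. For example, with 53% and 20%, p11 = 0.106 + 0.3 × 0.1996 = 0.166. Full capture gives b = 0.364 and c = 0.034; 80% capture gives b = 0.318 and c = 0.054.

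Power when capture is equal on both drugs:

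| True risks | 100% captured | 80% | 60% | 50% |
|---|---|---|---|---|
| 53% v 20% | 84% | 60% | 37% | 27% |
| 53% v 25% | 65% | 42% | 25% | 18% |
| 53% v 40% | 14% | 9% | 6% | 5% |

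False-positive rate when both true risks are 53% (p11 = 0.356):

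| Capture, drug 1 v drug 2 | Spurious difference | False-positive rate |
|---|---|---|
| 100% v 100% | 0 | 2.3% |
| 80% v 80% | 0 | 2.4% |
| 80% v 60% | 0.53 × 0.20 = 10.6 points | 9% |
| 90% v 50% | 0.53 × 0.40 = 21.2 points | 33% |

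**5. How far repeated contact helps.** If each of eight weekly contacts in a period independently caught a persistent effect 30% of the time (an assumption), capture would be 1 − 0.7^8 = 94%. At 95% capture, the 53% v 20% power is 78% instead of 84%. Dilution may therefore be small. This does not deal with unequal probing or grading.

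**The case against.** The strongest opposing case has four parts.

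- **Open questioning is an accepted method.** It limits suggestion by the interviewer, and the same approach is used in both periods. A checklist exchanges missed events for prompted ones. This stands: the method is not an error in itself, and equal under-capture cannot favour either drug.
- **It is not the sole source.** A reader might infer that side effects are gathered only by open questioning. The text contradicts that, because it adds volunteered reports, examinations, tests, other assessments and weekly monitoring. Still, volunteering shares the same weakness, laboratory tests do not detect dizziness or drowsiness, and nothing describes the weekly calls as using a fixed list.
- **A checklist may exist in the full protocol or case report form.** This also stands. An article need not print its forms, so the lack of a printed list is not the point. The point is the stated method, the comparative use of the record and the conflict over who collects it.
- **The power losses depend on chosen inputs.** A reader might take the fall from 84% to 27% as the trial's expected loss. The documents do not support that. No 20% or 25% risk appears in them, and the Background reports that side effects of the two drugs were probably similar. How the earlier cohort's 53% was elicited is not stated either, so it may already include under-reporting.

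It is also tempting to read the Discussion's remark that "PAGPROS may determine deficits and provide information not actually reported as SEs by the patients themselves" as an admission that the questioning is inadequate. In context it describes what the Health Locus of Control Scale is meant to add, and it is not evidence on this point.

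**Conclusion.** The point holds in a limited form. Non-directive questioning is suitable for surveillance, but here it is the main stated way of seeking events that also form the key between-drug secondary comparison. Data collection allows an unblinded person to gather that outcome, which conflicts with the blinded assessor under Randomisation and blinding. Probing and severity grading can therefore differ by drug.

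The documents establish a route to bias. They do not show that bias occurs, or in which direction. Neither the dilution nor any spurious difference can be sized from them; the tables above are illustrations under assumed inputs. The conclusion rests on reading Data collection as it is written, with the pharmacist's consultations as a place where secondary outcomes are recorded. If the full protocol assigns that task to a blinded person, the bias element falls away and only possible dilution remains.

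**What to change.** 1. Keep the open question first, for adverse-event reporting.
2. Then, at each scheduled side-effect time point in both periods, have the participant complete the same fixed checklist without the unblinded pharmacist's input. It should cover at least dizziness, drowsiness and decreased memory, each graded none, mild, moderate or severe.
3. Base the key secondary comparison on the checklist and report volunteered events separately.
4. Reconcile Randomisation and blinding with Data collection so that a blinded assessor collects and grades side effects. The pharmacist may still hear about side effects when handling doses, but should not record the outcome.

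**Cost.** One page at existing contacts, and a formal amendment. Solicited rates will be higher and less comparable with volunteered rates, which is why both are kept. Timing also matters. Trial status reports 18 participants already through the trial, so a checklist added at that point could cover at most 38 − 18 = 20. It should start only with participants who have not begun their first period, so that each person is asked in the same way on both drugs, and results should be shown by method of collection.

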### Modification of the protocol

Any modifications to the protocol that may impact the design and conduct of the study will require a formal protocol amendment. Such amendment will be agreed upon by the study investigators and approved by the local ethics committee prior to implementation. Once approved, the changes will be communicated to the relevant parties.

## Discussion

The PAGPROS protocol presents the design and rationale for a double-blind, double-dummy, randomised cross-over trial comparing the efficacy of PGB with GBP in treating CS. Owing to the variability in regular dosage frequency between the medications (PGB twice daily, GBP thrice daily), study medication packs will contain three bottles each, correlating to the dosage times of morning, lunchtime and night, to maintain blinding. Medication packs pertaining to the PGB arm will have placebo incorporated as the lunchtime dose, with all medications being indistinguishable.

Thus, PAGPROS represents the first head-to-head study to determine the relative role of either PGB or GBP in the evidence-based medical management of CS. However, in addition to efficacy, PAGPROS will also determine the frequency and severity of SEs with PGB or GBP. Thus, PAGPROS will determine the ‘efficacy versus SE trade-off’ with each drug and whether differences in compliance rates result in consequences. For example, in a prior study with GBP in treating CS, 31% of patients ceased GBP within 1 week of treatment [10]. Moreover, efficacy was significantly less in those who experienced SEs in that study [10].

In PAGPROS, we will employ the HLOC to assess psychological functioning with PGB or GBP in CS. In particular, PAGPROS will explore the prognosis of each drug relating to questionnaire outcomes relating to patients’ insight into their psychological dysfunction. Thus, PAGPROS may determine deficits and provide information not actually reported as SEs by the patients themselves. This may prove to be an important aspect of the study. For example, a prior prospective cohort study with GBP in treating CS revealed that, of 23 different SE types amongst 53% of patients, more than half could have adversely affected the ability to drive a motor vehicle safely or even to maintain employment [10].

Finally, the double-blind cross-over design of PAGPROS may provide guidance regarding the implications of any potential need to substitute one drug for the other. For example, PAGPROS may determine whether SEs experienced with one drug are also observed with the other (i.e., in the same patient, in close temporal succession after cross-over). This may prove especially important should PAGPROS demonstrate a between-groups null effect regarding efficacy. However, PAGPROS may show significant efficacy to one drug but no efficacy to the other. Despite a lack of an evidence base, many formulary regulatory authorities worldwide typically favour one drug for subsidy over the other [4]. This hinders interchange wherever the favoured drug is either ineffective or not tolerated [4]. The nature of PAGPROS’s design will directly assess the utility of cross-over between PGB and GBP and will therefore enable formulary regulatory authorities to make more informed therapeutic decisions than currently.

Recruitment commenced in early 2016, with data collection to be completed by mid 2018. The allocation concealment and double-blind design minimise bias, and data collection processes ensure data quality and integrity. The trial team has extensive experience in the design, conduct and reporting of clinical trials. Results of the study will be disseminated via publications and presentations.

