**Methods/design:**

We are conducting a prospective, randomised, double-blind, double-dummy cross-over study. Included patients will be over 18 years old and have unilateral CS with radiological confirmation of corresponding neural compression/irritation. Pregnant women, those with major organ disease, or those with creatinine clearance < 60 ml/minute will be excluded. Patients will continue their current pain medication at study onset, conditional upon dosage consistency during the prior 30 days. Each drug will be titrated up to a target dose (GBP 400–800 mg three times daily, PGB 150–300 mg twice daily) and taken for 8 weeks. The first drug will then be ceased; however, cross-over will be deferred pending a 1-week washout period. Drug efficacy will be assessed using the VAS and ODI. Results of the Health Locus of Control Scale and side effect frequency/severity will be used to determine psychological functioning. Assuming the hypothesis that PGB will display a superior effect, the sample size required is *n* = 38 with 80% power and a 5% type I error rate. Results will be analysed via intention-to-treat methodology.

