### Objectives

#### Primary objective and outcome

Our primary objective is to demonstrate if either GBP or PGB demonstrates superiority over the other in terms of efficacy for the treatment of patients diagnosed with CS. The co-primary outcome is leg pain intensity using a visual analogue scale (VAS) measured at baseline and at weeks 4, 8, 10, 14 and 18. The participants will be asked to rate their average leg pain over the last 24 h on a scale of 10, with zero representing ‘no leg pain’ and 10 representing the ‘worst pain imaginable’ [10].

The co-primary outcome is the Oswestry Disability Index (ODI) [10], measured at baseline and at weeks 4, 8, 10, 14 and 18, to assess disability. The Health Locus of Control Scale (HLOC) will also be used at baseline and at weeks 4, 8, 10, 14 and 18 to assess participants’ decision-making processes because we have identified compliance with these medications as being low [10].

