### Sample size

We hypothesise that over an 8-week treatment period, GBP will reduce pain on the VAS scale by an average of 4.5 points from (7.5 to 3.0) as per historical literature [16]. We predict PGB to show at least the same benefit. We hypothesise that PGB will display superiority over GBP by at least a 20% better relative reduction in VAS score, with a resultant reduction of 5.4 (from 7.5 to 2.1) points from baseline. This 20% relative reduction is based on the average reduction of pain symptoms compared with placebo for indirect comparisons [1, 16]. Relative reduction will be used because it is often more impressive and also to allow for the instance of a lower-than-expected event rate, which would lower the absolute risk reduction.

If the true difference in means of both arms of the study is 0.9 with an SD of 1.2, in order to detect this 20% relative decrease in pain between GBP and PGB, we will need to study 30 patients (15 per treatment arm) to reject the null hypothesis with 80% power. The type I error probability associated with this test of the null is 0.05. Assuming a 20% drop-out rate, the total sample size will be 38 patients (19 per treatment arm). We have chosen this large effect size and conservative SD on the basis of anecdotal and specialists’ experience with this cohort of patients. The benefits of the cross-over methodology are evident with the small sample size required, owing to each participant acting as his/her own control. If this were a conventional parallel study design, the sample size needed would be approximately 100 participants. We conservatively estimate that if two people can be recruited per week, the study duration will be approximately 1.5 years.

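### The HLOC is given conflicting purposes, and nothing in the protocol supports reading it as a measure of psychological functioning or of unreported side effects

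*Protocol article*

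**What the plan says.** The protocol article describes the role of the HLOC in three places.

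- **Objectives, Primary objective and outcome.** After naming VAS leg pain and the ODI as co-primary, the article adds the HLOC, with one measurement before treatment and five later ones (weeks 4, 8, 10, 14 and 18). Its stated target is "decision-making processes because we have identified compliance with these medications as being low".
- **Abstract, Methods/design.** "Results of the Health Locus of Control Scale and side effect frequency/severity will be used to determine psychological functioning".
- **Discussion.** The authors state that "we will employ the HLOC to assess psychological functioning with PGB or GBP in CS". They then tie the questionnaire results to how aware patients are of their own dysfunction and continue: "Thus, PAGPROS may determine deficits and provide information not actually reported as SEs by the patients themselves". They add that this may turn out to be an important part of the study. As an example they cite an earlier gabapentin cohort with 23 side-effect types among 53% of patients, many of them relevant to driving or work.

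Side effects have their own outcome. Under Secondary objective and outcome: "The key secondary outcome will be the record of frequency and severity of SEs". Under Adverse experiences and monitoring, events are graded mild, moderate or severe, and "The occurrence of adverse events should be sought by non-directive questioning of the patient at each visit during the study".

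**The concern.** One questionnaire is asked to inform two different things. Decision-making in the face of low compliance is a property of the patient that may explain who keeps taking the capsules. Psychological functioning on a drug is an effect of treatment. A score chosen for the first does not become evidence on the second unless something connects them, and the article offers no connection.

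The stake is what the trial may conclude. If the Abstract and Discussion are followed, a between-drug difference in HLOC could be written up as a difference in psychological functioning, or as a deficit that patients had not noticed. A null result could be written up as the absence of one. Neither conclusion would be supported. Effects such as dizziness (27%), drowsiness (22%) and decreased memory (20%), which the article lists under Secondary objective and outcome, are the kind of effect a reader would have in mind.

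**Working it through.** No arithmetic bears on this point. The only planned numbers, under Sample size, concern the VAS: "If the true difference in means of both arms of the study is 0.9 with an SD of 1.2", 30 evaluable patients, and 30 / 0.8 = 37.5, rounded up to 38 for drop-out. The HLOC plays no part in them. The check is therefore a comparison of the statements.

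1. **Construct.** The Objectives give decision-making, with low compliance as the reason. The Abstract gives psychological functioning, drawn from the HLOC together with side-effect frequency and severity. The Discussion gives psychological functioning with either drug, then patients' awareness of dysfunction, then deficits not reported as side effects. The last two places do not repeat the purpose in the Objectives, and no section reconciles them.

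2. **Link from score to deficit.** For the Discussion's inference to work, the article would have to say which HLOC result indicates a drug-related deficit, and why. It describes no items, scoring or direction for the scale, and it states no such link.

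3. **Other sources.** If another instrument measured cognition, mood or functioning, the HLOC could be supporting evidence. None is named. The Abstract's pairing with side-effect data does not fill the gap: a deficit that was not reported as a side effect cannot come from the side-effect record, so the HLOC alone would have to carry that inference.

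4. **Informant.** The HLOC is a questionnaire, and Data collection has outcomes gathered by telephone, email or online. The patient remains the source. The article describes no performance test or observer rating that could reveal what the patient does not report.

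5. **The supporting example.** The 23 side-effect types in the earlier cohort are presented as side-effect findings. Nothing says that the HLOC uncovered them. The example shows why a careful side-effect record matters, not that this scale detects hidden effects.

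6. **Reach.** The primary aim rests on VAS and ODI, and the key secondary outcome on the side-effect record. Neither uses the HLOC, so those comparisons stand whatever is done with it.

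**The case against.** The strongest reply is that the passage is modest. The sentence on deficits says only that the trial may find them, it stands in a Discussion, and the formal objectives contain no aim about hidden side effects. That is right, so a reader who infers that the protocol promises a conclusion about hidden side effects goes too far. The hedge does not cover everything, however: the Abstract says without qualification that the HLOC and side-effect results will be used to determine psychological functioning, and the Discussion says plainly that the HLOC will be employed for it.

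A second reply is that a scale can serve more than one purpose, and that the article never describes the HLOC's content. This also stands in part. The two uses need not exclude each other, and a flat statement that the scale cannot measure functioning would rest on outside knowledge of the instrument. The supportable statement is narrower: nothing in the document shows that it does.

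A third reply is that non-directive questioning may miss some effects, so looking beyond spontaneous reports is reasonable. The motive is sound, but it does not make the HLOC the tool for it.

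Finally, two further readings are tempting and not supported. Because the HLOC appears under the primary-outcome heading, it might be taken for a primary endpoint; only VAS and ODI are labelled co-primary. And a reader might infer a planned HLOC test at p < 0.05, or reassurance about driving drawn from a null result. The article gives only a general significance threshold without naming the HLOC, and states no such reassurance.

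**Conclusion.** The point holds as a contradiction of purpose and an unsupported inference. The Objectives and the Abstract and Discussion give the HLOC different constructs, and the article supplies no basis for reading its score as psychological functioning on a drug or as unreported deficits. Neither a between-drug difference nor its absence can carry such a conclusion.

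Its size cannot be put in numbers. It affects the interpretation of one questionnaire, scheduled six times per participant (baseline plus five later visits), and no conclusion on VAS, ODI or recorded side effects. It is worth correcting because it changes what the trial may claim.

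The verdict assumes that no cognition or mood instrument, and no validated link between the HLOC and drug effects, stands in a fuller protocol that is not shown. If one does, the inference might be defensible, but the differing statements of purpose would still need reconciling.

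**What to change.** - Keep the HLOC schedule as it is. Label the scale exploratory and list it apart from the co-primary VAS and ODI.
- Limit its interpretation to the purpose given in the Objectives, decision-making in relation to compliance. This can be examined against the medication diary and the counts of returned medicine, which Data collection already provides for. The form of that analysis is the authors' to specify; the article does not state one.
- Delete the statements in the Abstract and Discussion that the HLOC determines psychological functioning or may show unreported deficits, and do not carry them into the results report.
- Base conclusions on sedation, memory and similar effects only on the side-effect record, with its severity grades.

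The cost is small: changes of wording, and one exploratory claim withdrawn. With 18 participants reported as complete under Trial status and inclusion continuing, the interpretation can be settled before results are known. Dropping the post-baseline HLOC is neither needed nor only a matter of wording. It would change study conduct, require the amendment and ethics approval described under Modification of the protocol, and leave participants with unequal data.
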